### Collection of lifestyle data

Physical activity and sedentary habits will be determined using the Activity Profile – Spain – Version for Latin America (YAP-SL), a self-report tool consisting of 15 items, will be used to gather data on physical activity levels and sedentary behaviors for a 7-day recall period (23). The Spanish -language version validated for Latin America YAP questionnaire will be used (23). This instrument employs a 5-point Likert scale and is organized into three distinct sections: (1) school-related activities, (2) out-of-school activities, and (3) sedentary behaviors. First, school-related activities encompass transportation to and from the educational institution, participation in physical education classes, and engagement during lunch and recess periods. Second, out-of-school activities include those occurring prior to the school day, immediately following school hours, during the evening, and throughout the weekends, specifically on Saturday and Sunday. Third, sedentary habits include the duration of activities such as watching television, playing video games, using computers, and engaging with cell phones, in addition to a general measure of sedentary time. Additionally, recreational screen time will be assessed by asking adolescents to declare the time that they spent in different sedentary screen-based pursuits. The following questions will be asked for weekdays and weekends: (a) “How many hours a day, in your free time, do you usually spend watching TV, videos (including YouTube or similar services), DVDs, and other entertainment on a screen?”, (b) “How many hours a day, in your free time, do you usually spend playing games on a computer, games console, tablet, smartphone or other electronic device (not including moving or fitness games)?”, and (c) “How many hours a day, in your free time, do you usually spend using electronic devices such as computers, tablets or smartphones for other purposes (e.g., homework, emailing, tweeting, Facebook, chatting, browsing the internet)?”. A weighted sum of the three questions will be calculated (i.e., 5 weekdays and 2 weekend days).

Sleep duration will be assessed by asking about bedtime and wake-up time on both weekdays and weekends. For older children (8–18 years old), these data are self-reported with the following questions: “At what time do you usually go to bed?” and “At what time do you usually wake up?”. The mean daily sleep duration for each participant will subsequently be calculated on the basis of these responses via the following formula: [(average nocturnal sleep duration on weekdays × 5) + (average nocturnal sleep duration on weekends × 2)]/7. The responses were subsequently classified as “meeting sleep guidelines” if the participants presented the following sleep duration ranges according to age: 8–10 h for adolescents, 9–11 h for school-age children, 10–13 h for preschoolers, and 11–14 h for toddlers.

### Statistical analysis

The data from the PedsQL surveys will first undergo descriptive analysis by age group surveys for children and adolescents. Numerical variables will be summarized as mean and standard deviation for variables with a normal distribution or median and interquartile range for non-normally distributed variables. Categorical variables will be summarized as absolute and relative frequencies. This descriptive approach will provide an overview of the data and support subsequent analyses (see Supplementary Table 2 for details on variables and survey items).

To evaluate the primary research question regarding the impact of the physical activity program on HRQoL, a bivariate analysis will be conducted. The analysis will compare exposure to the physical activity program (intervention vs. control group) and the PedsQL survey scores at different time points (week 0, week 11, and week 24). For numerical variables with a normal distribution, the Student's t-test for independent samples will be used. For non-normally distributed variables, the Mann–Whitney *U* test will be applied. Additionally, to evaluate within-group changes over time (e.g., baseline vs. end of study), paired tests will be conducted using either the paired Student's t-test for normally distributed variables or the Wilcoxon signed-rank test for non-normally distributed variables.

An intention-to-treat analysis will be employed to ensure the robustness of the results and account for potential non-compliance or missing data. This approach will analyze participants based on their initial group assignment (intervention or control), regardless of adherence to the program or completion of all study components (22).

Statistical significance will be set at *p*-value < 0.05. All analyses will be performed using R Studio (R Project version 4.3.2).

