### Main outcome

This research focuses on assessing the HRQoL of pediatric cancer patients, emphasizing the relationship between structured exercise programs and improvements in well-being. HRQoL is defined, as per Dac and Abhishek, as the overall well-being of individuals, incorporating both positive and negative aspects of their lives at a specific point in time (13). Key dimensions include physical, mental, and spiritual health; relationships; education; sense of security; and general well-being (13).

To evaluate HRQoL, the study will use the PedsQL, specifically the PedsQL 3.0 Cancer Module, a validated instrument for pediatric cancer patients aged 2 to 18 years. Two age-appropriate versions will be administered, one for children aged 8–12 and another for adolescents aged 13- 18. This module comprises 20 questions addressing physical, emotional, and social functioning, as well as cancer treatment-related symptoms. Participants will self-report their responses using a four-point Likert scale, with options ranging from “never” (0) to “almost always” (4). For example: “In the past month, how often have you felt tired?”; “In the past month, how often have you experienced pain or discomfort?”.

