### Eligibility and randomization

This study will include participants aged 8–18 years. For study purposes, age groups will be categorized as follows:
•Children: Aged 8–12 years.•Adolescents: Aged 13–18 years (14).Participants will be randomized into one of two groups:
1.Intervention Group: Participates in a structured physical activity program.2.Control Group: Does not participate in the physical activity program.Randomization will be conducted using the REDCap randomization tool with allocation concealment ensured by restricting access to the randomization sequence (15). Medical oncologists involved in recruitment will not have access to group assignments at the time of enrollment. Additionally, the medical oncologist will be blinded for the group assignments, the social worker would know the group assignments for organization in participants for the physical activity program and surveys administered.

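### The primary comparison is an unadjusted two-group test that, on the natural reading, combines both age groups; adding age group and the week-0 score would be a nearly free gain in precision

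*Protocol article*

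**What the plan says.** Under Main outcome, the instrument is the PedsQL 3.0 Cancer Module: "Two age-appropriate versions will be administered, one for children aged 8–12 and another for adolescents aged 13- 18". Eligibility and randomization defines the same two bands ("For study purposes, age groups will be categorized as follows"). It names the REDCap tool for allocation and mentions no stratification factor.

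In Statistical analysis, age group appears in the descriptive step: "The data from the PedsQL surveys will first undergo descriptive analysis by age group surveys for children and adolescents". The inferential step does not mention it: "To evaluate the primary research question regarding the impact of the physical activity program on HRQoL, a bivariate analysis will be conducted". The comparison is then set out as arm against score: "The analysis will compare exposure to the physical activity program (intervention vs. control group) and the PedsQL survey scores at different time points". Two tests are named. The first is parametric: "For numerical variables with a normal distribution, the Student's t-test for independent samples will be used". The second is its rank-based substitute: "For non-normally distributed variables, the Mann–Whitney *U* test will be applied".

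Sample size calculation works out one two-arm comparison, with a target difference of 4.36, one common SD of 11.26, 95% confidence and 80% power. It arrives at 106 per group, or 133 after 20% loss, and then sets the actual sample at 90 in total, about 45 per group.

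**The concern.** Neither named test can carry a covariate. The plan treats age group as worth separating when scores are described, then drops it from the comparison that answers the trial's question. If mean scores differ between 8–12 and 13–18 year olds, two things follow.

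- The between-group variation stays in the residual and widens the interval for the arm difference.
- Without stratified allocation, the arms may by chance hold different proportions of adolescents, and the estimate is not adjusted for that.

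If allocation does use age group as a stratum, the unadjusted standard error is somewhat too large for the design, and the test rejects less often than its nominal level. In each case the information needed to do better is already collected. A trial cut from 133 to about 45 per group for budget reasons has little precision to spare.

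**Working it through.** **Inputs from the protocol.** Difference 4.36, SD 11.26, 80% power, 1:1 allocation, 20% loss, 90 participants (Sample size calculation); significance level 0.05 (Statistical analysis). The SD is taken as stated.

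**Inputs assumed.** The protocol gives neither the age split nor the mean score difference D between age groups. I use a 50:50 split and D = 3, 5 and 8 points, with D = 0 as the null case.

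**1. The plan's own figure.** n per arm = 2(1.960 + 0.842)² × 11.26² / 4.36² = 104.7, so 105 by the normal approximation; the noncentral t gives 106. With 20% loss, 106 / 0.80 = 132.5, so 133. Both stated figures reproduce with a two-sided test (one-sided gives 83). So the calculation sizes a single two-group comparison with one SD and no covariate.

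**2. Power at the actual size, unadjusted.** SE = 11.26 × √(2/45) = 2.374; 4.36 / 2.374 = 1.837; power = Φ(1.837 − 1.960) = 45.1%. At 36 per arm (45 × 0.80) it is 37.6%.

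**3. What an age-group term removes.** With a 50:50 split, the variance share is R² = (D/2)² / 11.26² and the residual SD is 11.26 × √(1 − R²).

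| Assumed D | R² | Residual SD | Power, 45 per arm | Power, 36 per arm | Equivalent extra participants, 1/(1 − R²) − 1 |
|---|---|---|---|---|---|
| 0 | 0 | 11.26 | 45.1% | 37.6% | 0 |
| 3 | 2.25/126.79 = 1.8% | 11.16 | 45.7% | 38.1% | 2% |
| 5 | 6.25/126.79 = 4.9% | 10.98 | 47.0% | 39.2% | 5% |
| 8 | 16/126.79 = 12.6% | 10.53 | 50.2% | 42.0% | 14% |

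At D = 5 and 45 per arm, the 95% CI half-width falls from 1.960 × 2.374 = 4.65 to 1.960 × 2.315 = 4.54.

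**4. Chance imbalance without stratification.** With 90 participants, 45 of them adolescents, and 45 per arm, the adolescent count in one arm is hypergeometric. The difference in adolescent share has SD 0.106. It is at least 15 percentage points in about 21% of allocations and at least 20 points in about 9%. The shift in the arm contrast is D times that difference. At D = 5 this is 0.75 to 1.0 point at those imbalances; over all allocations its SD is 5 × 0.106 = 0.53, against a standard error of 2.37.

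**5. Validity of the unadjusted test.** In simulation without stratification (40,000 trials per setting, D = 0, 5 and 10, at 45 and 36 per arm), its type I error was 4.8% to 5.1%. If allocation is stratified on age group and the test ignores it, the true two-sided error is about 2[1 − Φ(1.96/√(1 − R²))] = 4.8%, 4.4% or 3.6% for D = 3, 5 or 8.

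**6. The week-0 score for comparison.** With an assumed correlation of 0.5 to 0.7 between baseline and follow-up, residual SD = 11.26 × √(1 − ρ²), and power at 45 per arm is 56% to 73%. On these assumptions the baseline score gains more than age group does.

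**The case against.** The strongest reply is that nothing here is invalid. Randomisation makes the unadjusted contrast unbiased, and its standard error already allows for chance imbalance in age. The shifts in step 4 are conditional on tail allocations. A reader might infer that a different mix of questionnaire versions biases the programme effect or inflates false positives. The documents do not support that, and step 5 shows the error rate holds. This reply stands in full.

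A reader might also infer that two incompatible scales are being added together. That is not supported either: Main outcome describes one module with one item count, one set of domains and one response scale for both versions. Nothing says the versions score differently.

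Next, pooling is never stated in words. Design says the schedule allows comparison between the two age groups, and tests could in principle be run within each version. That is possible but less natural, because the sample size calculation plans a single two-arm comparison. Separate tests would leave about 22 to 23 per arm and roughly 25% power for 4.36.

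Finally, the size of the gain is assumed and may be zero, the study calls itself a pilot, and a condensed article may leave stratification factors to the full protocol. All of that is fair, so silence on stratification is not criticised here. What survives is that the article does name the primary tests, and those tests exclude any covariate.

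**Conclusion.** The point holds as a modest efficiency gain, not as an error. On the natural reading, the primary test combines both age groups without adjustment, when a better method is available at almost no cost. Age group alone would add between 0.6 and 5.1 percentage points of power at 45 per arm (45.7 − 45.1 and 50.2 − 45.1) for assumed differences of 3 to 8 points, and nothing if the groups do not differ. It would also protect against an unlucky age mix. These figures rest on the stated SD of 11.26, an assumed 50:50 age split and assumed age-group differences. Including the week-0 score in the same model is likely to matter more. This belongs among the free improvements to consider and does not threaten the trial's validity.

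**What to change.** In Statistical analysis, replace the bivariate test with a linear model of the follow-up PedsQL score (week 11, and likewise week 24) on arm, with age group (8–12 / 13–18) and the week-0 score as covariates. Report the common arm difference with its 95% CI.

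The cost is one degree of freedom per covariate (with 90 participants, 90 − 2 = 88 becomes 90 − 4 = 86) and no new data, since age and the week-0 survey are already collected. If age group proves unrelated to score, the loss is negligible.

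Using age group as a REDCap stratification factor is optional and applies only if allocation has not started. The model serves under either allocation scheme.

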## Material and methods

### Design

This study is designed as a randomized controlled trial to investigate the impact of a structured exercise program on the HRQoL of pediatric cancer patients. A total of 90 participants will be recruited and randomly assigned to either the intervention group or the control group.

The intervention group will participate in a 10-week structured physical activity program consisting of 120 min of supervised exercise per week, led by a team of physiotherapists and physical activity professionals from Hospital Sociedad de Lucha Contra el Cáncer del Ecuador (SOLCA) Quito. Meanwhile, the control group will not participate in any organized physical activity program but will continue with their usual activities. As part of the evaluation process, two versions of the Pediatric Quality of Life Inventory (PedsQL) survey will be administered: one tailored for children aged 8–12 and another for adolescents aged 13–18. Both groups will complete their respective surveys at three time points—baseline (week 0), post intervention (week 11), and follow-up (week 24). This approach allows for the assessment of changes in HRQoL over time and enables comparative analysis between the two age groups.

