## Discussion

Although the study sample size is constrained by budgetary limitations and is smaller than initially calculated, this research represents a valuable first step toward evidence generation in a neglected population and geographic context. The findings will contribute preliminary insights on the feasibility, safety, and potential effectiveness of a structured physical activity program in pediatric cancer care in Ecuador. These results may serve as a foundation for designing larger multicenter trials and for informing public health policy in similar low-resource environments. A key strength of this study is its use of repeated measures, which allows for the tracking of HRQoL changes over time at multiple points (week 0, week 11, and week 24). This approach provides a robust understanding of the temporal impact of the intervention, capturing both short- and long-term benefits. Additionally, this study is the first of its kind in Ecuador, addressing a critical gap in the literature on pediatric cancer care within the region. By focusing on a structured and accessible program, this study seeks to establish a scalable model that can be adapted to meet the needs of a broader pediatric population. The ultimate goal is to inform and enhance the design of care programs that are inclusive, sustainable, and capable of significantly improving the reach and quality of care for pediatric patients, particularly in resource-constrained settings.

This research serves as a foundational step for future studies and public health initiatives, encouraging further exploration of pediatric HRQoL not only in Quito but across Ecuador. By providing evidence-based insights into the effectiveness of physical activity programs, this study offers a critical framework for developing hospital-based interventions tailored to the unique needs of pediatric cancer patients. These findings have the potential to guide the expansion of such programs at a national level, addressing the disparities in pediatric cancer care in Ecuador and beyond.

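### The between-arm tests of PedsQL never adjust for the baseline score, and change is tested only within each arm, which gives up precision in a trial already short of power

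*Protocol article*

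**What the plan says.** The Statistical analysis section of the protocol article assigns the primary question to a bivariate analysis that will "compare exposure to the physical activity program (intervention vs. control group) and the PedsQL survey scores at different time points"; the time points are weeks 0, 11 and 24. For normally distributed scores, "the Student's t-test for independent samples will be used". Otherwise: "For non-normally distributed variables, the Mann–Whitney *U* test will be applied". Neither test takes a covariate.

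Change over time has a separate provision: "to evaluate within-group changes over time (e.g., baseline vs. end of study), paired tests will be conducted", by paired t-test or Wilcoxon signed-rank test.

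The article mentions no ANCOVA, mixed model, arm-by-time term or between-arm comparison of change. Yet the Design section has both arms complete the survey at baseline, week 11 and week 24, and the Discussion states: "A key strength of this study is its use of repeated measures, which allows for the tracking of HRQoL changes over time at multiple points".

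**The concern.** The three visits allow each child's starting score to be used when the arms are compared. The stated analysis uses that score in two other ways. It tests the arms against each other at week 0, where randomisation already makes the null hypothesis true. It also uses the score as the reference for paired tests inside each arm. Neither use estimates the effect of the programme.

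Two things are at stake. The first is precision. The Sample size calculation section asks for 106 per group, or 133 with losses, and the trial will enrol about 45, so an efficient analysis matters more than usual. The sample also mixes children on treatment with children in post-treatment follow-up, so scores may vary widely at entry. The second is interpretation. Paired tests reported arm by arm invite the conclusion that the programme works because one arm improved significantly and the other did not. That conclusion does not follow from those tests.

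**Working it through.** **Inputs.** From Sample size calculation: difference 4.36, common SD 11.26, power 80%, 1:1 allocation, 20% loss, about 45 per group enrolled. From Statistical analysis: significance level 0.05, taken as two-sided. Completers: 45 × 0.80 = 36 per arm. The correlation ρ between baseline and follow-up scores is not given, so it is an assumption, shown from 0.3 to 0.8. The SD is assumed equal at all visits.

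**The plan's own figure.** n per arm = 2 × [11.26 × (1.960 + 0.842) / 4.36]² = 104.7, so 105. The noncentral-t version gives 106, as stated, and 106 / 0.80 = 132.5, so 133, as stated. The sizing is that of an unadjusted two-sample comparison and takes no credit for baseline.

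**Power with and without baseline.** ANCOVA multiplies the outcome variance by 1 − ρ², so the residual SD is 11.26 × √(1 − ρ²) and 36 per arm act like 36 / (1 − ρ²). Power for 4.36 points (noncentral t, 36 per arm):

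| ρ (assumed) | Variance factor | 36 per arm act like | Power |
|---|---|---|---|
| unadjusted | 1.00 | 36 | 37% |
| 0.3 | 0.91 | 40 | 40% |
| 0.5 | 0.75 | 48 | 46% |
| 0.7 | 0.51 | 71 | 62% |
| 0.8 | 0.36 | 100 | 77% |

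With no losses (45 per arm) the corresponding powers are 44%, 48%, 55%, 72% and 86%.

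**Chance imbalance at baseline.** The SE of the week-0 difference with 45 per arm is 11.26 × √(2/45) = 2.37. The chance that it exceeds 2.18 (half of 4.36) in either direction is 36%; the chance that it exceeds 4.36 is 7%. The expected carry-over into follow-up is ρ times the imbalance. For 2.18 points that is 0.65 at ρ = 0.3, 1.09 at 0.5 and 1.53 at 0.7.

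**Within-arm paired tests.** Suppose both arms truly change by the same amount, so that there is no treatment effect. If each paired test is significant with probability p, exactly one arm is significant with probability 2p(1 − p), which cannot exceed 50%. The SD of change is 11.26 × √[2(1 − ρ)]. With 36 per arm:

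| Common change (assumed) | ρ = 0.3 | ρ = 0.5 | ρ = 0.7 |
|---|---|---|---|
| 0 | 9.5% | 9.5% | 9.5% |
| 2 | 24% | 29% | 39% |
| 3 | 39% | 45% | 50% |
| 4.36 | 50% | 47% | 28% |
| 6 | 38% | 22% | 4% |

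**A between-arm t-test of change scores.** Its variance factor is 2(1 − ρ), which is above 1 whenever ρ is below 0.5. At ρ = 0.3 the factor is 1.40 and power with 36 per arm is 28%, lower than the 37% with no adjustment.

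**The case against.** The strongest reply is that the planned test is sound. In a randomised trial an unadjusted comparison at week 11 or 24 is unbiased, and its type I error rate already allows for chance imbalance. That stands. A reader might infer that the result would be biased or invalid, or that a baseline imbalance passes in full into the follow-up difference. The documents support neither; the carry-over is only in proportion to ρ.

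Second, the gain depends on a correlation that the documents do not give. At ρ = 0.3 it is about three percentage points of power. With 36 completers per arm no value up to 0.8 reaches 80%. Adjustment improves the trial but does not make up for its size.

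Third, it goes too far to say that the repeated measures are discarded. The paired tests use them, and the Discussion claims only that they track change. The primary question is assigned to the between-arm comparison and the paired tests are an addition, so the misreading is a risk and not a planned inference. Its frequency is near 50% only for some assumed changes.

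Fourth, the article calls the study a pilot, and Limitations discloses reduced power. This lowers the severity. It does not remove the point, because the plan still tests effect at p < 0.05, and preliminary data for a larger trial are more useful when the difference is estimated more precisely.

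That a statistical analysis plan may exist is no answer: the article states the method and does not leave it open.

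**Conclusion.** The point holds as a loss of efficiency and a risk to interpretation. As written, the primary comparison makes no use of a baseline score that every child provides, and the only tests of change do not compare the arms. With 36 completers per arm, adjustment would raise power for 4.36 points from about 37% to between 40% and 77% for assumed correlations of 0.3 to 0.8. Where both arms change equally, the within-arm tests would be significant in exactly one arm in roughly 4 to 50% of trials (assumed change 0 to 6 points, correlation 0.3 to 0.7).

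These figures take the SD of 11.26 as given. The formula printed beside it, 15 × √(1 − 0.85), gives 5.81, so the SD cannot be derived as described, and every power and imbalance figure here would move with it. The relative gain in variance, 1 − ρ², would not.

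This should be fixed, but it is not a fatal flaw: the planned test is valid and the study describes itself as a pilot.

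**What to change.** Rewrite the between-arm paragraph of the Statistical analysis section before outcomes are compared by arm:

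- Make the primary analysis an ANCOVA of the week-11 PedsQL score on arm and week-0 score, with the same model for week 24. Alternatively, fit one mixed model with weeks 11 and 24 as outcomes and week 0 as a covariate only, not also as an outcome visit.
- Report the adjusted mean difference with its 95% CI. If residuals are skewed, use robust or bootstrap standard errors and do not switch to a rank test, so that the estimate stays on the scale of the 4.36-point difference used for sizing.
- Drop the week-0 significance test between arms. Report within-arm changes descriptively, without p-values.
- Age group and treatment status are recorded and may be added as covariates. This is optional; the core fix needs only the baseline score.
- Do not substitute a plain t-test of change scores, which is less precise than no adjustment when the correlation is below 0.5.

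The cost is one rewritten paragraph, with no extra participants, visits or data.

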### Sample size calculation

The sample size calculation for this study was conducted considering a confidence level of 95%, a power of 80%, equal variances between groups, and a 1:1 ratio between sample sizes. The difference in means to be detected was set at 4.36, based on literature identifying this value as the minimum clinically significant difference (17). The common standard deviation was calculated at 11.26, using the formula for the standard error of measurement (SEM = 15 × √1−0.85), where the Cronbach's alpha reliability coefficient is 0.85. The formula for hypothesis testing by comparing means of independent groups was applied using the Epidat 4.2 program, resulting in a required sample size of 106 participants per group. To account for an estimated 20% loss to follow-up, the sample size was increased to 133 participants per group. However, due to budgetary limitations, the final study sample will consist of a total of 90 participants (approximately 45 per group). While this is lower than the 160 participants initially estimated through power calculations, this adaptation reflects real-world constraints commonly encountered in resource-limited settings. The study is therefore best positioned as a pilot randomized controlled trial, with the aim of generating preliminary data to inform future larger-scale interventions.

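### The primary question is tested at both week 11 and week 24 at p < 0.05 with no score or visit named as primary, so even one score carries a false-positive chance of about 7–10%, although the trial is sized for one comparison

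*Protocol article*

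**What the plan says.** - **Statistical analysis** sets out how the main question is to be answered: "To evaluate the primary research question regarding the impact of the physical activity program on HRQoL, a bivariate analysis will be conducted". The two arms are compared on "PedsQL survey scores at different time points (week 0, week 11, and week 24"), by t-test or Mann–Whitney test. The section then adds tests inside each arm: "to evaluate within-group changes over time (e.g., baseline vs. end of study), paired tests will be conducted". One threshold serves everything: "Statistical significance will be set at *p*-value < 0.05". No adjustment, ordering or split into primary and secondary is given. Age groups appear in this section only in the descriptive step.
- **Main outcome** names the PedsQL 3.0 Cancer Module and describes its content: "This module comprises 20 questions addressing physical, emotional, and social functioning, as well as cancer treatment-related symptoms". It designates neither a total nor a domain score as primary, and no visit.
- **Sample size calculation** rests on one two-group comparison of means, "considering a confidence level of 95%, a power of 80%, equal variances between groups, and a 1:1 ratio between sample sizes", with a difference of 4.36 and a standard deviation of 11.26. It does not say to which score or visit the 4.36 points belong. It then cuts the sample to 90 for budget reasons and describes the trial as a pilot.
- **Design** adds that the survey schedule "enables comparative analysis between the two age groups", without naming a test.

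**The concern.** The sample size assumes one test, while the analysis applies the same test at two visits after the program. Nothing says whether success means an effect at week 11, at week 24, at either or at both. Under the either-visit reading, which the text allows, the 5% threshold is not the error rate for the primary question, and the visit to be emphasised can be chosen once the data are seen.

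The wording elsewhere does not settle the visit. The paired-test sentence mentions the end of the study, but Study duration gives 18–22 weeks in total, which is the 8–12 weeks of recruitment plus the 10-week program and leaves no room for a week 24 survey. The Discussion presents both the short-term and the longer-term result as things the trial will show.

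The outcome is self-reported, and the Limitations section accepts that participants and assessors cannot be blinded. An endpoint fixed in advance is one of the few safeguards left.

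**Working it through.** **1. The plan's own figure.** Inputs from Sample size calculation: difference 4.36, SD 11.26, 95% confidence, 80% power, 1:1 allocation. Two-sided testing is assumed because it reproduces the stated result.

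n per group = 2 × (1.960 + 0.842)² × 11.26² / 4.36² ≈ 104.7, so 105 by the normal formula. The t-based version gives 105.7, so 106. Then 106 / 0.80 = 132.5, so 133. Both stated figures (106 and 133 per group) are reproduced, and both are for one comparison at 0.05.

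**2. Tests that can show a program effect.** Three visits are listed. Week 0 precedes the program, so a difference there cannot be claimed as its effect. That leaves two between-arm tests, weeks 11 and 24, for one score.

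**3. Chance of at least one false positive, one score at two visits.** Assume no true effect at either visit and each test two-sided at 0.05.

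- Independent tests: 1 − 0.95² = 0.0975.
- Correlated tests: 1 − P(|Z₁| ≤ 1.96 and |Z₂| ≤ 1.96), with Z₁ and Z₂ bivariate normal. The documents give no correlation between visits, so a range is assumed:

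| Assumed correlation | Chance of at least one false positive |
|---|---|
| 0 | 9.75% |
| 0.5 | about 9.0% |
| 0.7 | about 8.4% |
| 0.9 | about 7.0% |

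The correlated rows come from simulation with 200,000 draws. Direct integration of the bivariate normal agrees to within 0.1 percentage point. The rate is therefore about 1.4 to 2 times the nominal 5%.

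**4. After the change.** With one score at one visit named, the error rate for the primary claim is 5% by construction, and 106 and 133 per group remain the matching sizes. If both visits stayed primary at 0.025 each, the normal formula would need 127 per group before dropout.

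**5. Power at the actual size, for the same 4.36 and 11.26.** After 20% loss, 45 per group becomes 45 × 0.80 = 36.

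| Primary test | 45 per group | 36 per group |
|---|---|---|
| One visit at 0.05 | about 45% (t-based 44%) | about 38% (t-based 37%) |
| Two visits at 0.025 each | about 34% | about 27% |

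Splitting the error rate over two visits is thus a costly alternative to choosing one.

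**The case against.** **Pilot status.** The article positions the trial as a pilot that generates preliminary data, and strict control of the error rate matters less for that purpose. This stands in part: it lowers the consequence. It does not remove it, because the Statistical analysis section still tests a primary question at p < 0.05 and the Conclusion speaks of evidence for bringing such programs into routine care.

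**A separate analysis plan.** Multiplicity rules are often left to an analysis plan, and the article is silent on adjustment; it does not say that there will be none. That is fair for domain scores and subgroups. It is weaker for the primary endpoint, because the article does state the primary analysis, and states it as tests at several visits against one threshold.

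**Modest size.** On the narrow reading the rate is 7–10%. This stands, and it is the size claimed here.

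**Stronger readings that a reader might infer.**

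- *Many scores are tested.* Four domain scores at two visits would give 1 − 0.95⁸ = 34% if independent, or about 21–30% with assumed correlations of 0.3–0.7 between scores and 0.5–0.7 between visits. But the plural in the analysis section also fits one score per participant, two age versions or three visits, and Main outcome describes what the questions cover, not which scores are tested. The supplementary table on variables and survey items is not at hand.
- *Age groups are tested at 0.05.* One score at two visits, tested separately in each age group, would give about 16–17%. But Statistical analysis treats age groups descriptively, and Design only says that a comparison is possible.
- *Week 0 adds to the error.* It does not, for the reason given in step 2 of the working.

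**Conclusion.** The concern holds in its narrow form. The primary question is tested between arms at two post-baseline visits, no score or visit is named as primary, and the sample size is for one comparison. For one score the chance of at least one false-positive effect is about 7–10% instead of 5%.

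This assumes no true effect at either visit, a claim allowed on either visit, no adjustment in a document not shown, and a between-visit correlation from 0 to 0.9. A higher figure would need domain-score or age-group tests that the article does not clearly specify. The within-arm paired tests are not in this figure. They are a further route to an apparent effect, and they are not randomised comparisons.

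The point is worth correcting before data are seen, but given the pilot aim it does not invalidate the trial.

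**What to change.** - In **Main outcome** and **Statistical analysis**, name one primary endpoint, for example the between-arm difference in the PedsQL Cancer Module total score at week 11, after the program ends, with all ages pooled, tested at 0.05. The choice of score and visit is the sponsor's; what matters is that it is fixed beforehand.
- In **Sample size calculation**, say that the 4.36 points refer to that score and visit.
- Make week 24 and any domain scores secondary, reported as estimates with 95% confidence intervals, or tested with Holm adjustment.
- Treat week 0 as a description of the arms, and label any age-group comparison and the within-arm paired tests exploratory or descriptive.

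**Cost:** a few sentences. Data collection and the planned two-group tests are unchanged, and the primary test keeps its 0.05. The downside is that week 24 and domain scores can no longer support a stand-alone claim. If the sponsor wants week 24 to carry equal weight, the split at 0.025 shown in the working is the alternative, with the lower power given there.
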